### Intervention

#### Psychoeducational Intervention Program (“Komuniti Sihat”)

“Komuniti Sihat,” which means “A Healthy Community,” is a brief Web-based psychoeducational intervention program. It was developed based on the findings from the first phase of this study, which explored the predictors of depression [22] and anxiety in the community of Selangor, Malaysia. The predictors of depression and anxiety were the presence of chronic diseases, serious problems at work, serious financial constraint, high perceived stress, domestic violence, low self-esteem, and unhappy relationships with children, spouse, and family. These predictors were incorporated in the program.

The intervention program consists of four sessions, with each session accessed each week. The first session includes a description of depression and anxiety, facts and myths, causes, symptoms, available treatments, self-help tips, and contact information for help. The second session involves some CBT and positive psychology. This session includes: what we need to understand, why we need to change our thinking, what we need to do, ways to think positive, ways to solve problems, relaxation techniques, and general ways to achieve good mental health. The third and fourth sessions are mainly to address stressful life events based on the findings from the first phase of the study. The third session is on techniques on how to deal with chronic diseases, stress, low self-esteem, and domestic violence, whereas the fourth session deals with issues of unhappy relationships with spouse and children, financial constraints, and problems at work.

A pilot study was carried out among 40 participants before data collection in February 2014. Errors and mistakes in the program were identified through comments obtained from the participants and were corrected accordingly. The content of this program was also reviewed by a group of expert panels, including a family medicine specialist, two psychiatrists, two clinical psychologists, a public health physician, an epidemiologist, and a biostatistician. The content of the program was revised and refined based on the comments and suggestions received from the expert panel and were also modified to meet our target population. The development of the program, process of reviewing, amendments, and completion of the program took 8 months to complete.

The four-session program is delivered online on a weekly basis. It takes approximately 15 to 20 minutes to complete each session. The participants will be taught on how to log on and use the website during the first visit to their respective households. Participants’ email addresses will be registered by an information technology technician based on the allocation group. Thereafter, the participants will log on to the website [23], using their email addresses and passwords, and complete the assessments and sessions on their own. Participants in the intervention group are allowed to view the full content on the website and use the program as frequently and as long as they want. The researchers can monitor each participant’s detailed log-in information in the back-end system.

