### Waitlist Control Group

Participants allocated to the control group will be blocked from the content of the intervention program. They will only be allowed to do the assessments. After the 12-week follow-up assessment, the participants in the control group will be offered to join the intervention program if they are interested and this is purely on a voluntary basis.

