#### Secondary Outcome Measure

The secondary outcome of this study will be the change in the mental health literacy score. This is defined by a change in the total score on the Mental Health Literacy Questionnaire (MHLQ) between the baseline and follow-up assessments at weeks 5 and 12 (Table 1).

**Table 1 table1:** Overview of measurements.

Instrument	Aim	Time of measurement		
		T_0_ (Baseline)	T_1_ (Posttest at week 5)	T_2_ (Follow-up at week 12)
Sociodemographics	Characteristics of participant	Yes		
PHQ-9	Symptoms of depression	Yes	Yes	Yes
GAD-7	Symptoms of anxiety	Yes	Yes	Yes
MHLQ	Mental health literacy	Yes	Yes	Yes

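### As written, only the intervention arm can consult the course content while answering the week-5 and week-12 literacy questionnaire, so its score may mix look-up with learning

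*Protocol article*

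**What the plan says.** The relevant statements are spread over five Methods sections of the protocol article.

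- **Mode of assessment** (Psychoeducational Intervention Program): after logging in, participants "complete the assessments and sessions on their own". The test is unsupervised and on the same site as the course.
- **Intervention access** (same section): this arm may view all the content and "use the program as frequently and as long as they want". No closing date is given, and nothing says that content is hidden during an assessment.
- **Control access** (Waitlist Control Group): the rule for this arm reads "Participants allocated to the control group will be blocked from the content of the intervention program". Its use of the site is limited in the same place: "They will only be allowed to do the assessments". The block covers both follow-up tests: "After the 12-week follow-up assessment, the participants in the control group will be offered to join the intervention program".
- **Outcome** (Secondary Outcome Measure): the "change in the total score on the Mental Health Literacy Questionnaire (MHLQ) between the baseline and follow-up assessments at weeks 5 and 12".
- **Items** (Mental Health Literacy Questionnaire): 12 yes/no items summed to a score of 0 to 12. Eight were written from the programme's content and four were adapted from an existing questionnaire.
- **Timing** (Recruitment): the baseline assessment comes before randomisation.

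**The concern.** Unequal access to the course is the treatment being tested. Unequal access to the course while the test is being answered is a difference in measurement conditions, and the two can be separated. Under the stated rules, an intervention participant can have the source of eight items open beside the questionnaire, and a control participant cannot. A correct answer that was looked up scores the same as one that was known.

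Because baseline precedes randomisation, access does not differ between the arms at baseline. Any look-up advantage arises only at weeks 5 and 12, so it enters the change score in full. What is at stake is the reading of the stated secondary outcome: a between-arm gain on MHLQ could be partly look-up, and a gain still present at week 12 could be taken for retained knowledge when the pages may still have been open.

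The limitations part of the Discussion considers whether the right person completes the study and relies on a personal login. That does nothing about look-up by the right person.

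**Working it through.** **Step 1. Conditions at each MHLQ assessment, as written**

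| | Baseline | Week 5 | Week 12 |
|---|---|---|---|
| Intervention arm: course content | not yet randomised | open (no limit or lock stated) | open (no limit or lock stated) |
| Control arm: course content | not yet randomised | blocked | blocked |
| Supervision, both arms | none | none | none |
| Items developed from the content | 8 of 12 | 8 of 12 | 8 of 12 |

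The two follow-up tests differ by arm and the baseline test does not. The entry *open* is inferred from unlimited use with no stated end or lock. The article does not say it outright.

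**Step 2. Is there a plan figure to reproduce?** No. The article gives no expected MHLQ score, no MHLQ SD and no look-up rate. Its sample size calculation uses another scale and does not bear on this point. What follows is an illustration only.

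**Step 3. Shift from look-up alone**

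Assumptions: no true learning; a share *f* of the intervention arm looks up all eight content-derived items and gets all of them right; everyone else answers a proportion *p* correctly; controls look nothing up.

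Shift = *f* × 8 × (1 − *p*)

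At *p* = 0.6 this is *f* × 8 × 0.4 = 3.2*f*:

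- *f* = 0.10: 0.32 points
- *f* = 0.30: 0.96 points

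With an assumed SD of 2.0 to 2.5, the smallest standardised value is 0.32 / 2.5 = 0.13 and the largest is 0.96 / 2.0 = 0.48.

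**Step 4. Sensitivity to the unaided score**

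| *p* | Shift per unit *f* | Points, *f* = 0.10 to 0.30 | SD units (SD 2.5 at the low end, 2.0 at the high end) |
|---|---|---|---|
| 0.5 | 4.0 | 0.40 to 1.20 | 0.16 to 0.60 |
| 0.6 | 3.2 | 0.32 to 0.96 | 0.13 to 0.48 |
| 0.8 | 1.6 | 0.16 to 0.48 | 0.06 to 0.24 |

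**Step 5. What such a shift could do to a test**

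Take a simple two-sided comparison of two means at 0.05, with 64 per arm (the article's number before the dropout allowance). Rejection probability ≈ Φ(*d*√(64/2) − 1.96).

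- *f* = 0.10, *p* = 0.6: shift 0.32, *d* = 0.13 to 0.16, rejection probability about 11% to 15%.
- *f* = 0.25, *p* = 0.6: shift 0.80, *d* = 0.32 to 0.40, rejection probability about 44% to 62%.

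These probabilities carry the same assumptions as Step 3, and they are not the power of the planned mixed ANOVA.

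**The case against.** The strongest reply has five parts.

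1. *Open content at weeks 5 and 12 is read from silence.* The permissive phrase stands beside text on weekly sessions and could describe use during the programme only. A journal article may also leave site settings to the full protocol. This stands as a limit on certainty. But the article does state the access rules for both arms: a block with a stated end for controls, and use without a stated end for the intervention arm. Followed as written, the conditions differ.

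2. *Controls are not tested without aids.* They too are online, Internet-literate and unsupervised, and may search elsewhere. This stands. A reader might infer an open-book test in one arm and a closed-book test in the other. The documents do not support that; the asymmetry concerns the course content only.

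3. *The problem is not independent of where the items came from.* This largely stands. A reader might infer that any item set would be equally exposed, but the exposure comes mainly from the eight items written from the course.

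4. *The size is assumption.* This stands. Look-up may be rare, since nothing in the article rewards a high score. The assumption that every looker gets all eight right is generous. An SD of √(12 × 0.6 × 0.4) = 1.70, from independent and equally hard items, would enlarge the standardised effect to 0.19 to 0.57, but positively correlated items give a larger SD, so that range is too favourable to the concern.

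5. *The outcome is a score, not unaided recall, and the Introduction counts repeated home access as an advantage.* The outcome definition indeed claims no unaided recall. That limits how the result may be described, and it does not make the test conditions equal.

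**Conclusion.** The point holds as a modest improvement to one secondary outcome. As written, the follow-up MHLQ is taken with the course content available to one arm and barred to the other. Any resulting bias favours the intervention and cannot be separated from learning in the total score. The illustrative 0.32 to 0.96 points (about 0.13 to 0.48 SD) rests wholly on assumed values for look-up rate, unaided score and SD, and on no look-up by controls.

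Two stronger readings are not supported. The documents do not show that anyone looked up answers, so MHLQ cannot be called invalid or its week-12 value meaningless. Nor is there a threat to the primary outcomes by this route: PHQ-9 and GAD-7 are symptom scores with no answers to find in the course.

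**What to change.** **For any use of the site still to come:** lock session content for an account from the time a week-5 or week-12 assessment falls due until it is submitted, then reopen it. State this under Psychoeducational Intervention Program and under Secondary Outcome Measure. The site already blocks content for controls, so the change should be small. The cost is a short loss of access for intervention participants until they submit.

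**For data already collected** (the Results section says collection was complete at submission): report the four adapted items separately from the eight content-derived items as a sensitivity analysis, and do not describe week-12 MHLQ as retained, unaided knowledge. This needs no new data. Its limits should be stated: a four-item score is imprecise, and a larger effect on the eight items would fit true learning as well as look-up.

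**Not advised:** setting items to missing for intervention participants who viewed content near the test. That selects on post-randomisation engagement in one arm, could discard the answers of people who did learn, and needs page-view data where the article mentions only log-in information.

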#### Emails and Text Messages

Before commencement of the program, the participants will be notified of the dates for each session through email, which will also be provided in the website log-in information site. Participants will receive notification of the commencement of each session every Monday via email and a phone call and they will be given 7 days to complete the session. First reminders via text messages will be sent every Wednesday to alert the participants to log in and complete the session. For those who do not complete the session, a second and third reminder through phone calls will be done on Fridays and Sundays. These reminders are important to enhance the compliance of the participants to the program.

### Waitlist Control Group

Participants allocated to the control group will be blocked from the content of the intervention program. They will only be allowed to do the assessments. After the 12-week follow-up assessment, the participants in the control group will be offered to join the intervention program if they are interested and this is purely on a voluntary basis.

### Outcome Measures

#### Primary Outcome Measure

The primary outcome of this study will be the change in depressive and anxiety symptoms. This is defined by a change in the sum score on the Patient Health Questionnaire 9 (PHQ-9) and Generalized Anxiety Disorder 7 (GAD-7) between the baseline and follow-up assessments at weeks 5 and 12.

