**Methods:**

A two-arm randomized controlled trial of a single-blind study will be conducted to meet the objective of this study. We aim to recruit 84 participants each for the intervention and control groups. The recruitment will be from participants who participated in the first phase of this research. The primary outcomes of this study are depressive and anxiety scores, which will be assessed using the Patient Health Questionnaire 9 and Generalized Anxiety Disorder 7, respectively. The secondary outcome includes mental health literacy of the participants, which will be assessed using the self-developed and adapted Mental Health Literacy Questionnaire. The psychoeducational intervention program consists of four sessions, which will be accessed each week. The depressive and anxiety symptoms will be compared between participants who participated in the psychoeducational program compared with the control group. Depressive and anxiety scores and mental health literacy will be assessed at week 1 and at follow-ups at week 5 and week 12, respectively.

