**Results:**

The psychoeducational intervention program consists of four sessions, which will be accessed at each week. The depressive and anxiety symptoms will be compared between the intervention and control groups using a series of mixed ANOVAs. Depressive and anxiety scores and mental health literacy will be assessed at week 1 and at two follow-ups at week 5 and week 12, respectively.

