### Sample Size

The sample size for this study was calculated using a formula by Lemeshow et al [29]: n=(2σ^2^[Z_1−α/2_+Z_1−β_]^2^)/([μ_1_−μ_2_]^2^).

Using a power of 80%, a confidence interval of 95%, a pooled standard deviation of 9.865, and a baseline and posttest mean score of 21.1 and 16.2, respectively, in the intervention group [11], the calculated sample size was estimated to be 64 participants. Taking into consideration a 30% dropout rate [30], the final sample size calculated was 84 participants in each group.

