### Statistical Analysis

Data will be analyzed using IBM SPSS version 21.0 software. Differences between sociodemographic characteristics for the intervention and control groups will be tested using chi-square and *t* tests. A mixed between-within subjects ANOVA will be employed to compare the mean difference of the psychoeducation intervention program between the two groups at pretest, posttest (week 5), and at 2-months of follow-up (week 12). The magnitude effect size of the intervention program will be calculated using Cohen’s formula. Analyses will be conducted based on the intention-to-treat principle and for all completers.

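### Two unranked primary scales with no success rule are set against a sample size for one 5% comparison, so 5% error and 80% power cannot both hold until the scales are ranked

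*Protocol article*

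**What the plan says.** The Abstract (Methods) puts the primary outcomes in the plural: "The primary outcomes of this study are depressive and anxiety scores, which will be assessed using the Patient Health Questionnaire 9 and Generalized Anxiety Disorder" (that is, GAD-7). The Primary Outcome Measure section uses the singular, "The primary outcome of this study will be the change in depressive and anxiety symptoms", and then counts changes in both sum scores "between the baseline and follow-up assessments at weeks 5 and 12". Neither scale is placed above the other, and neither follow-up is singled out.

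The Abstract (Results) says that symptoms will be "compared between the intervention and control groups using a series of mixed ANOVAs". The Statistical Analysis section describes the model: "A mixed between-within subjects ANOVA will be employed to compare the mean difference of the psychoeducation intervention program between the two groups at pretest, posttest" at week 5 and follow-up at week 12. One model per scale therefore takes all three time points together.

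The Sample Size section uses the formula for comparing two means: "Using a power of 80%, a confidence interval of 95%, a pooled standard deviation of 9.865", with means of 21.1 and 16.2. It arrives at 64 per group, and at 84 after a dropout allowance. This is the only place where an error level appears.

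**The concern.** The sample size treats the trial as having one confirmatory comparison, while the outcome definition gives it two scales of equal standing. The article does not say what result would count as effectiveness, and each possible rule breaks one of the two design figures. If either scale suffices at 5%, the chance of a false claim exceeds 5%. If alpha is divided, or both scales must succeed, power falls below 80%.

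The Abstract (Conclusions) says that the results will determine whether the programme is effective and could support its use as a new way of managing these disorders. Without a stated rule, emphasis could settle on the more favourable scale or visit after the results are known. Timing adds to this. The Results section reports that data collection is complete, the Trial section says only that analysis was not yet finished, and the Randomization section says that the researcher in charge knows the allocation.

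**Working it through.** **Inputs from the article.** SD 9.865; difference 21.1 − 16.2 = 4.9; two-sided alpha 0.05 (from the 95% level and the Z term at 1 − α/2); power 80%; two primary scales; two follow-ups. The article gives no correlation between PHQ-9 and GAD-7 or between visits, so all correlations below are assumptions.

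**1. The article's own figure.** n = 2σ²(Z₁₋α/₂ + Z₁₋β)²/(μ₁ − μ₂)² = 2 × 9.865² × (1.960 + 0.842)²/4.9² = 194.64 × 7.849/24.01 = 63.6, rounded up to 64. The stated figure is reproduced with one two-sided 5% test and no allowance for a second.

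**2. Either scale suffices, one group-by-time test per scale.** If the scales are independent, the error is 1 − 0.95² = 9.75%. Simulation of two correlated 2-df group-by-time tests (1,000,000 draws, large-sample) gives:

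| Between-scale correlation (assumed) | Chance of at least one false positive |
|---|---|
| 0 | 9.7% |
| 0.5 | 9.2% |
| 0.7 | 8.4% |
| 0.8 | 7.9% |

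This is 1.6 to 1.95 times the 5% level.

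**3. Each follow-up also tested separately (four tests).** If all four are independent, the error is 1 − 0.95⁴ = 18.5%. By simulation, with correlations given as between scales/between visits: 16.2% at 0.5/0.5, 13.7% at 0.7/0.7 and 12.8% at 0.8/0.7. Counting both the group term and the group-by-time term on each scale gives a similar range, 17.4% to 15.1% at between-scale correlation 0.5 to 0.8.

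**4. Alpha halved (0.025 per scale).** The standardized difference is 4.9/9.865 = 0.497. With 64 per group the expected test statistic is 0.497 × √(64/2) = 2.81. Power is Φ(2.81 − 1.960) = 80.2% at alpha 0.05 and Φ(2.81 − 2.241) = 71.5% at alpha 0.025. Restoring 80% at alpha 0.025 needs 78 per group before dropout.

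**5. Both scales must succeed.** The error cannot exceed 5%. Assuming the same standardized effect on both scales, joint power at 64 per group is 0.802² = 64% at correlation 0, 69% at 0.5 and 72% at 0.7 (bivariate normal).

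**The case against.** The strongest objection concerns the number of tests. A reader might infer that four quantities, two scales at two visits, are each tested at 5%, so that false claims run at two to three times the stated level or more. The Statistical Analysis section does not support this. Its mixed ANOVA takes both follow-ups into one model, so a second visit does not by itself add a test, and the series of ANOVAs fits one model per scale. On the natural reading there are two tests, and the inflation is a little under double. The 13% to 18.5% range needs separate visit tests, which the article neither clearly plans nor rules out.

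A reader might also infer that a single p<0.05 on either scale would be declared a success. No such rule is written. The article joins depressive and anxiety symptoms with 'and', so requiring both is an open reading, and under it there is no inflation at all.

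Finally, the deciding model term and any adjustment for multiplicity are commonly left to an analysis plan, which is not shown here. Their absence from a condensed article is not the defect.

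These points limit the size of the problem but do not remove it. The article itself fixes two primary scales of equal rank and a calculation for one comparison. An unseen adjustment would not bring those two statements into line unless it ranked the scales.

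**Conclusion.** The concern stands in limited form. As written, the plan cannot deliver both 5% overall error and 80% power, because it has two unranked primary scales and a single-test sample size. The size depends on the success rule, which is not stated:

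- **Either scale suffices:** error of about 8% to 9.75%, rising to about 13% to 18.5% only if the follow-ups are tested separately as well.
- **Alpha halved:** power of about 71.5% at 64 per group.
- **Both required:** error at or below 5%, joint power of about 64% to 72%.

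The error rates rest on assumed correlations (0 to 0.8 between scales, 0 to 0.7 between visits). The joint power rests on equal standardized effects and a between-scale correlation of 0 to 0.7. All power figures use the article's own two-mean formula, its SD and its difference, with 64 per group analysed. They are not calculated for the group-by-time test itself. This should be corrected because it changes what the trial may claim, but it does not show that the planned model is wrong.

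**What to change.** Keep the planned mixed ANOVA and add a short rule to the Statistical Analysis section:

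1. Name the group-by-time test as the deciding test for each scale.
2. Control two-sided 5% across the two scales, by one of two routes. Either test in fixed order with PHQ-9 first, since the Introduction describes the sample-size source as a study of depressive symptoms, or apply Holm to the two tests.
3. Report the week 5 and week 12 contrasts as supportive, with 95% confidence intervals.
4. In the Sample Size section, state that 80% power applies only to the first-ranked test or, under Holm, restate it as about 72% at the first step.
5. Date the rule and state what data and results had been seen when it was set. With data collection complete and the allocation known to the researcher in charge, a rule added now cannot simply be presented as prespecified.

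The cost is about a paragraph and a dated statement, and the model does not change. Under the fixed order, no GAD-7 claim is possible if PHQ-9 fails. Under Holm, either scale can succeed alone, but the stated power is lower. A visit-by-visit testing sequence is not needed and would replace the planned model.
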